## Abstract

**Background:**

Benfotiamine provides an important novel therapeutic direction in Alzheimer’s disease (AD) with possible additive or synergistic effects to amyloid targeting therapeutic approaches.

**Objective:**

To conduct a seamless phase 2A-2B proof of concept trial investigating tolerability, safety, and efficacy of benfotiamine, a prodrug of thiamine, as a first-in-class small molecule oral treatment for early AD.

**Methods:**

This is the protocol for a randomized, double-blind, placebo-controlled 72-week clinical trial of benfotiamine in 406 participants with early AD. Phase 2A determines the highest safe and well-tolerated dose of benfotiamine to be carried forward to phase 2B. During phase 2A, real-time monitoring of pre-defined safety stopping criteria in the first approximately 150 enrollees will help determine which dose (600 mg or 1200 mg) will be carried forward into phase 2B. The phase 2A primary analysis will test whether the rate of tolerability events (TEs) is unacceptably high in the high-dose arm compared to placebo. The primary safety endpoint in phase 2A is the rate of TEs compared between active and placebo arms, at each dose. The completion of phase 2A will seamlessly transition to phase 2B without pausing or stopping the trial. Phase 2B will assess efficacy and longer-term safety of benfotiamine in a larger group of participants through 72 weeks of treatment, at the selected dose. The co-primary efficacy endpoints in phase 2B are CDR-Sum of Boxes and ADAS-Cog13. Secondary endpoints include safety and tolerability measures; pharmacokinetic measures of thiamine and its esters, erythrocyte transketolase activity as blood markers of efficacy of drug delivery; ADCS-ADL-MCI; and MoCA.

**Conclusion:**

The BenfoTeam trial utilizes an innovative seamless phase 2A-2B design to achieve proof of concept. It includes an adaptive dose decision rule, thus optimizing exposure to the highest and best-tolerated dose.

**Trial registration:**

ClinicalTrials.gov identifier: NCT06223360, registered on January 25, 2024. https://classic.clinicaltrials.gov/ct2/show/NCT06223360.

## Introduction

Alzheimer’s disease (AD) is a progressive age-associated neurodegenerative disease. It is the most common cause of dementia and has devastating socioeconomic implications. More than 5 million people are afflicted with AD and related dementias in the United States, and by 2050 this number could rise as high as 16 million, with annual costs of over $1 trillion [1]. The potential to preserve, or even improve, cognition in adults at high risk of cognitive decline due to AD clearly has important implications, not only for the affected individual, but also for the support system that bears the social and financial burdens of long-term caregiving. Despite recent advances in amyloid targeting therapies, they do not address processes that are upstream and downstream of the amyloid cascade. Thus, complementary therapies that address these processes are needed.

Benfotiamine a prodrug of thiamine provides a novel therapeutic direction in AD that has potential for additive or synergistic effects beyond current mainstream approaches. It is a first-in-class small molecule with a unique mechanism of action, that raises blood thiamine (vitamin B1) 50–100 times to pharmacological levels. In this way, it addresses and treats a well-characterized tissue thiamine action deficiency in AD that is associated with changes in glucose metabolism and thiamine dependent post-translational modifications that are linked to AD pathology. This includes action on the α-Ketoglutarate Dehydrogenase Complex (KGDHC)-regulated succinylation of the TCA cycle that links brain glucose metabolism to AD pathophysiology [2]. These related post translational modifications have been identified on tau and Abeta with effects that have been shown to promote plaque and tangle formation [3], neuroinflammation [4,5], neurodegeneration [2], and increased advanced glycation end products (AGE) [6] which are regulated by thiamine. AGE are toxic modifications that form by the chemical addition of glucose and its byproducts to proteins, lipids and nucleotides when glucose is not tightly controlled in the cell, as is seen with the abnormal glucose metabolism in AD. High concentrations of AGE are predictive of long-term decline in cognition-related daily living performance in patients with AD [7]. Whereas thiamine deficiency increases AGE, increasing brain thiamine activates transketolase, which diminishes AGE [8,9].

CNS thiamine deficiency and its effects on memory and cognition have been well known since 1930s [10]. It is the cause of the amnestic disorder of the Wernicke-Korsakoff syndrome [10] with data strongly supporting its pathogenetic role as well in AD. Thiamine dependent processes are deficient in autopsied brains from AD patients including transketolase (controls the pentose phosphate pathway), the pyruvate dehydrogenase complex [PDHC, links glycolysis to the tricarboxylic acid cycle (TCA)], glyoxalase (detoxification of AGE precursors) and KGDHC (controls the TCA cycle) [11,12]. Furthermore, the reduced thiamine dependent enzyme activity measured in post-mortem brain tissue in AD patients, correlates with pre-mortem degree of impairment on the Clinical Dementia Rating (CDR) score [13]. Preclinical studies using a range of models including isolated proteins, cell systems and animal models demonstrate that thiamine deficiency stimulates many AD-like pathological changes including amyloid plaque and tangle formation, neuronal loss, inflammation, oxidative stress, cholinergic deficits, abnormally reduced glucose metabolism and memory deficits [14].

Recent data provides a mechanistic framework for the decline in thiamine-dependent processes in the brains of patients with AD. Thiamine entry into the brain is controlled by transporters and the transporters are diminished in autopsied brains from AD patients and in brains from mouse models of AD [15]. High concentrations of thiamine in the serum such as those induced by benfotiamine can overcome a reduction in transporters [16]. Model systems studies have demonstrated that high thiamine achieved by increasing dosages of benfotiamine reverses AD-like changes including restoring thiamine-dependent enzymes, with improvement in brain glucose metabolism, in reducing plaques [17] and tangles [3], neuroinflammation [4,5] neurodegeneration [2], and reducing AGE [6].

These preclinical studies have supported a small, single-site 12-month pilot trial of benfotiamine in persons with early AD (35 per treatment arm) that demonstrated benfotiamine is safe and well tolerated with encouraging PK and PD responses [6]. The treatment delivery of benfotiamine in a dose of 600 mg/d achieved its intended PK outcome with a 161-fold mean increase in blood thiamine. The trial also provided preliminary evidence of efficacy of benfotiamine on cognitive and functional outcomes. While group difference in change on the Alzheimer’s Disease Assessment Scale-Cognitive Subscale (ADAS-Cog) did not reach statistical significance, there was a numerical benefit, with 43% less decline in benfotiamine (-1.39) vs placebo (-3.26) (mixed effect model p = 0.071, GEE p = 0.137, and non-parametric Wilcoxon rank sum test p = 0.098). The CDR, a composite of cognition and everyday function, showed a significant benefit (p = 0.034), and other measures showed favorable treatment effects on patterns of brain glucose utilization (p = 0.002) and patterning scores (p = 0.0329) on ^18^F-fluorodeoxyglucose positron-emission tomography (FDG PET). Plasma AGE, marking pharmacodynamic target engagement, were also reduced in a randomly selected subset of patients (p = 0.044) [6]. In this study there was a pattern of pharmacogenomic response where participants without *APOE* ε4 were more responsive to benfotiamine than those with *APOE* ε4.

These preliminary results justify the testing of benfotiamine in a larger seamless phase 2A-phase 2B randomized controlled trial (RCT) to investigate its safety, tolerability, and efficacy in early AD [18]. The BenfoTeam trial will provide the next level of necessary clinical, safety and efficacy evidence to establish “Proof of Concept” (POC) for benfotiamine.

## Materials and methods

### Objectives

The primary objective of phase 2A is to determine the highest safe and well-tolerated daily dose of benfotiamine (600 mg/d or 1200 mg/d), as evaluated by the rate of tolerability events (TEs), to advance to the longer-term phase 2B study. The secondary objective of phase 2A is to evaluate additional measures of safety and tolerability of 600 mg/d or 1200 mg/d doses of benfotiamine.

The primary objective of phase 2B is to assess the efficacy of benfotiamine on global function and cognition over 72 weeks. The secondary objectives of phase 2B are to evaluate: 1) longer-term safety and tolerability of benfotiamine treatment, 2) the effects of benfotiamine’s PK relationships to primary clinical outcome measures, (plasma thiamine, and thiamine esters in whole blood, thiamine diphosphate (ThDP) and thiamine monophosphate (ThMP) and erythrocyte transketolase activity), and 3) benefits of benfotiamine on everyday activities of daily living and specific aspects of cognitive function (e.g., memory) over 72 weeks.

Exploratory objectives of phase 2B are to evaluate: 1) the downstream biological effects of treatment with benfotiamine on measures of neurodegeneration (cortical thickness MRI, plasma neurofilament light chain, total tau), neuroinflammation (plasma glial fibrillary acid protein) and AD pathophysiology (plasma p-tau231, p-tau217, Aβ 42/40, p-tau217/np-tau217(p-tau217 ratio) over 72 weeks, 2) the effects of benfotiamine on neuropsychiatric symptoms and cognitive-functional composite measures, 3) the effects of benfotiamine on remotely-administered measures of cognition, and to compare the sensitivity of remote and in-person cognitive assessments, and 4) the relationship between PK measures, including plasma thiamine, thiamine esters in whole blood (ThDP and ThMP), erythrocyte transketolase activity, and PD measures including AGE.

### Design

This overall design is a placebo controlled parallel group RCT over 72 weeks. The Phase 2A safety and dose selection decision will be reached when either 21 total TEs have been observed across both the high dose arm and the placebo arm, or when 160 person-months of exposure have accumulated in each of the high dose and placebo arms, whichever comes first (see S1 File). If the tolerability stopping rule is not reached by this predetermined number of TEs, the 1200 mg dose will continue, the 600 mg dose will be titrated upwards, and randomization will be adjusted for the remainder of trial enrollment to be 1:1 active versus placebo across the trial population. The completion of phase 2A will seamlessly transition to phase 2B without pausing or stopping the trial. Phase 2B will assess efficacy and longer-term safety of benfotiamine at the selected dose in a larger group of participants through 72 weeks of treatment.

The schedule of enrollment, interventions, and assessments is shown in Fig 1. The study schematic is shown in Fig 2.

**Fig 1 pone.0302998.g001:**
[figure not shown]
Schedule of enrollment, interventions, and assessments. Abbreviations: ECG, electrocardiogram; TSH, thyroid stimulating hormone; PK, pharmacokinetic; PD, pharmacodynamic; AGE, advanced glycation end products; ThDP, thiamine diphosphate; ThMP, thiamine monophosphate; Nfl, neurofilament light chain; GFAP, glial fibrillary acidic protein; Aβ, beta-amyloid; MRI, magnetic resonance imaging; CSF, cerebrospinal fluid; LP, lumbar puncture; CAGE-AID, CAGE Adapted to Include Drugs; C-SSRS, Columbia Suicide Severity Rating Scale; MoCA, Montreal Cognitive Assessment; MMSE, Mini-Mental State Examination; CDR, Clinical Dementia Rating; ADAS-Cog13, Alzheimer’s Disease Assessment Scale-Cognitive Subscale 13; ADCS-ADL-MCI, Alzheimer’s Disease Cooperative Study–Activities of Daily Living Scale for use in Mild Cognitive Impairment; NPI, Neuropsychiatric Inventory; IP, investigational product.

**Fig 2 pone.0302998.g002:**
[figure not shown]
Study schematic. Abbreviations: BF, benfotiamine; OD, every day; DSMB, Data Safety Monitoring Board.

### Participants

This trial (NCT06223360) will include 406 participants with early AD, including participants with MCI or mild dementia due to AD according to NIA-AA Diagnostic Criteria with a positive plasma AD biomarker test result (C_2_N PrecivityAD2; APS2 value >47.5) [19–22]. Key inclusion criteria include aged 50–89, Mini-Mental State Examination (MMSE) total score 20–30, Montreal Cognitive Assessment (MoCA) <26, and CDR score of 0.5 or 1 with memory score of ≥ 0.5 at screening. A complete list of inclusion criteria is presented in Table 1. Key exclusion criteria include any significant neurological or neurodegenerative disorder (other than AD), uncontrolled depression or major depression, a current diagnosis of uncontrolled type I or type II diabetes mellitus, a diagnosis of cancer (unless no evidence of recurrence for 5 years), any other major psychiatric disorder or active medical condition that impairs cognition or impacts participation, MRI at screening shows evidence of infection, tumor, cortical infarction, or multiple lacunes in prefrontal or critical memory regions, and initiation of a monoclonal antibody treatment targeting brain amyloid (including lecanemab, aducanumab, solanezumab, donanemab) within 6 months. A list of exclusion criteria is presented in Table 2. Recruitment and enrollment of participants will occur through the Alzheimer’s Disease Cooperative Study (ADCS) network at approximately 50 sites in the United States. A list of participating sites can be viewed at www.clinicaltrials.gov.

**Table 1 pone.0302998.t001:** Inclusion criteria.

Inclusion criteria	
1.	Aged 50 to 89 (inclusive) at screening.
2.	Mild Cognitive Impairment due to AD or Mild probable AD (NIA-AA^1^^,^^2^).
3.	Mini-Mental State Examination (MMSE) score 20–30 inclusive at screening.
4.	Montreal Cognitive Assessment score (MoCA) < 26 at screening.
5.	Clinical Dementia Rating (CDR) global score of 0.5 or 1 with memory score of ≥ 0.5 at screening.
6.	Positive plasma AD biomarker signature: Plasma test (C_2_N PrecivityAD2). To qualify participants will have a High Amyloid Probability Score (APS2 >47.5). If previously treated with any anti-amyloid monoclonal antibody (AAMA) and C2N PrecivityAD2 is negative, documentation of a pre-AAMA treatment positive amyloid status with either amyloid PET, CSF, or appropriate plasma test.
7.	Stable dosage of AchEIs and/or memantine for at least 3 months prior to screening.
8.	Availability of a study partner who has frequent interaction with the participant (approximately >3–4 times per week) and is available for all study visits.
9.	For FDA-approved monoclonal antibodies targeting brain amyloid (including lecanemab, aducanumab, solanezumab, donanemab), participants must be on stable dose of treatment for at least 6 months prior to screening.
10.	Women must be post-menopausal for at least one year or surgically sterile (bilateral tubal ligation, hysterectomy, or bilateral oophorectomy) for at least 6 months prior to screening.
11.	Fluent in English or Spanish.
12.	Living in the community (includes assisted living facilities).
13.	Ambulatory, or able to walk with an assistive device.
14.	Informed consent from the participant (or the participant’s legally authorized representative if lacking decisional capacity), as well as study partner consent.

Note.

^1^ Albert, M.S., et al., The diagnosis of mild cognitive impairment due to Alzheimer’s disease: recommendations from the National Institute on Aging-Alzheimer’s Association workgroups on diagnostic guidelines for Alzheimer’s disease. Alzheimers Dement, 2011. 7(3): p. 270–9.

^2^ McKhann, G.M., et al., The diagnosis of dementia due to Alzheimer’s disease: Recommendations from the National Institute on Aging-Alzheimer’s Association workgroups on diagnostic guidelines for Alzheimer’s disease. Alzheimer’s & Dementia, 2011. 7(3): p. 263–269.

**Table 2 pone.0302998.t002:** Exclusion criteria.

Exclusion Criteria	
1.	Significant neurological disorder other than AD including hypoxia, stroke, traumatic brain injury.
2.	Diagnosis of uncontrolled depression or major depression, as determined by DSM-IV, unless successfully treated.
3.	Any other major psychiatric disorder that impairs cognition or impacts participation in the study is exclusionary. Participants with major psychiatric disorders (e.g., severe generalized anxiety disorder, bipolar disorder, schizophrenia etc.) where the condition is felt to be the most significant contributor to the cognitive impairment should be excluded.
4.	Active medical conditions that impair cognition or impact participation in the study, other than AD should be exclusionary. Participants with medical conditions (e.g., severe obstructive sleep apnea) in whom the condition is felt to be the most significant contributor to the cognitive impairment should be excluded.
5.	Significant neurodegenerative diseases, other than AD, and other causes of dementias.
6.	A current diagnosis of uncontrolled type I or type II diabetes mellitus, as defined by Hemoglobin A1 C (Hb A1C > 8).
7.	A current active, uncontrolled seizure disorder.
8.	Participation in another clinical trial for an investigational agent of: Symptomatic medications, participation is excluded within 4 weeks prior to the screening visit. Disease-modifying medications, participation is excluded within 6 months of the screening visit.
9.	Previous exposure to benfotiamine within past 3 months.
10.	Current serious or unstable medical illness that could interfere with the interpretation of safety and assessment of efficacy in this study.
11.	Diagnosis or treatment of cancer within the past 5 years.
12.	History of alcoholism or substance abuse, current or within past 5 years.
13.	Contraindication to MRI.
14.	MRI at screening showing evidence of infection, tumor, cortical infarction, or multiple lacunes in prefrontal or critical memory regions.
15.	Initiation of an FDA-approved monoclonal antibody treatment targeting brain amyloid (including lecanemab, aducanumab, solanezumab, donanemab) within 6 months prior to the screening visit.
16.	A disability that may prevent the patient from completing all study requirements in the opinion of the PI.

### Concomitant medications

Use of the following medications is prohibited throughout participation in the study: thiamine or benfotiamine supplements outside of a multivitamin, immunosuppressive medications, chemotherapeutic agents for malignancy, or any concomitant treatment which may impair cognitive function. Medications that are central nervous system active (e.g., hypnotics) and may affect cognitive function are not permitted for 72 hours prior to neuropsychological testing.

Eligible participants being treated with FDA-approved acetylcholinesterase inhibitors (AchEI) and/or memantine at the time of screening are expected to remain on a stable dosage regimen of these medications for the duration of the trial. They may be initiated as clinically indicated during the study when a participant is not already on these medications at the outset, with appropriate documentation. FDA-approved monoclonal antibodies targeting brain amyloid are permitted, but participants must be stable for at least 6 months on such treatment prior to screening. For medications not intended to treat AD, participants must be on a stable dose for at least 4 weeks prior to baseline, except for medications which are administered for a short course of treatment.

### Interventions

Benfotiamine capsules, 300 mg, 600 mg, or placebo are provided as opaque dark green (chlorophyll) colored capsules for oral administration. The placebo group will receive capsules with microcrystalline cellulose, with all other components, shape, and color identical to the active treatment. Participants are assigned capsules twice a day (BID; once in the morning and once in the evening). Participants receive a new supply for each dosing period between study visits and are provided a diary to track daily intake and timing of dose. During study visits, participant investigational product (IP) supply will be assessed for compliance.

### Randomization and blinding

A randomization schedule will be generated and incorporated into an electronic Randomization and Trial Supplies Management (RTSM) system. The treatment group will be assigned as the site randomizes the participant. In phase 2A of the trial, as shown in Fig 2, each participant will be randomly allocated in a 1:1:1 ratio into one of the 3 groups: 1200 mg/d benfotiamine, 600 mg/d benfotiamine or placebo. At the dose decision point that ends phase 2A, all participants enrolled in the two phase 2A active dose arms will receive a new supply of benfotiamine at the selected highest tolerable dose for phase 2B. An unscheduled visit at the start of phase 2B may be required to replace IP supply in all active participants once the phase 2A dose selection is made. Newly enrolled participants will be randomized 1:2 active arm to placebo arm until parity is achieved between numbers of active and placebo arm participants (approximately 150 participants total), randomized 1:1 thereafter (approximately 100 participants). In both phases of the trial, the randomization will be stratified by site.

Participants and study personnel will be blinded to both treatment arm and dosage. There will be provisions for the site Principal Investigator (PI) to unblind treatment assignment in consultation with the ADCS Medical Monitor only in the case of an emergency.

### Adverse events

All AEs (i.e., a new event or an exacerbation of a pre-existing condition in its frequency or severity) that occur from the time of consent and up to 30 days after the IP has been discontinued will be recorded. A treatment emergent AE (TEAE) is defined as any AE that developed, worsened, or became serious after first dose of IP and prior to 30 days after the last dose of IP. A serious adverse event (SAE) is an AE that results in any of the following outcomes: death, life-threatening situation (participant is at immediate risk of death), inpatient hospitalization or prolongation of existing hospitalization, persistent or significant disability/incapacity, congenital anomaly/birth defect in the offspring of a patient who received IP, or considered significant by the investigator for any other reason. All AEs will be followed until resolution or until the Investigator and/or the Medical Monitor determine the event is chronic or clinically stable.

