#### Phase 2B secondary safety and tolerability endpoints

Secondary safety and tolerability endpoints for phase 2B include: 1) number of participants with AEs/TEAEs and SAEs 2) number of participant withdrawals from the study, and 3) number of participants discontinuing IP.

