### Early discontinuation

The entire study may be otherwise discontinued at the discretion of the ADCS or the study PIs ([name], [name], [name]) for administrative or other reasons. Participants are free to withdraw from study participation at any time, for any reason, and without prejudice. Discontinuation of study treatment and/or the participation of an individual patient can occur in the following circumstances: 1) withdrawal of informed consent by the participant or legally authorized representative (LAR), 2) treatment with a non-permitted concomitant medication, 3) AE or other significant medical condition which, in the opinion of the Investigator, render it necessary to discontinue study drug, 4) medical emergency that necessitates unblinding the participant’s treatment assignment, 5) any other occurrence that, in the PIs opinion, makes continued participation contrary to the participant’s best interest, or 6) movement of the participant into a long-term care nursing facility. Participants who discontinue study treatment for any reason will have the opportunity to continue on the protocol to the end of the study with their ongoing consent.

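### Adverse event recording ends 30 days after study drug is stopped, although participants who stop drug may remain on study to week 72, so their later SAEs and deaths fall outside the stated recording rule

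*Protocol article*

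**What the plan says.** The Adverse events section of the protocol article sets one collection window: all AEs "that occur from the time of consent and up to 30 days after the IP has been discontinued will be recorded". The TEAE definition in the same section ends at essentially the same point, covering events "after first dose of IP and prior to 30 days after the last dose of IP". Seriousness does not lengthen the window, because an SAE is defined as a subset of AEs: "A serious adverse event (SAE) is an AE that results in any of the following outcomes: death", followed by the other usual outcomes.

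The Early discontinuation section keeps people in the trial after they stop drug: "Participants who discontinue study treatment for any reason will have the opportunity to continue on the protocol to the end of the study", subject to their continuing consent. The Design section fixes the length of follow-up: "This overall design is a placebo controlled parallel group RCT over 72 weeks".

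Longer-term safety is a secondary objective of phase 2B (Objectives). The matching secondary endpoints include the "number of participants with AEs/TEAEs and SAEs", together with study withdrawals and discontinuations of study drug.

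**The concern.** A cut-off of 30 days after the last dose is a usual way to define an on-treatment event. Here it also limits what is collected, while some of the participants concerned are still attending visits. The primary efficacy model (Statistical analyses, Phase 2B) uses all available outcomes, so the week 72 scores of someone who stopped drug early but stayed would be analysed. An SAE in the same person over the same months would not have to be recorded.

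Two things are at stake. First, the safety data over 72 weeks are incomplete for participants who stop drug. Second, the window closes at an event that happens after randomization and can itself be caused by safety problems: Early discontinuation lists an adverse event or significant medical condition among the grounds for stopping treatment, participation or both. If one arm stops more often than the other, its recording time is shorter and its counts of recorded events are lower for that reason alone.

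**Working it through.** **Is there a longer window elsewhere?** Three places in the article could supply one.

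- Adverse events also says: "All AEs will be followed until resolution or until the Investigator and/or the Medical Monitor determine the event is chronic or clinically stable". This governs how long a recorded event is followed, not the period in which a new event qualifies.
- Safety surveillance calls for monitoring of AEs, TEAEs and SAEs in both phases. It sets no window of its own and no separate rule for participants off drug.
- Ethics has sites notify the central IRB of SAEs, with no time frame. That is a reporting duty to the IRB, not capture in the trial database.

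None extends the window for SAEs or deaths.

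**Inputs from the article.** Follow-up T = 72 weeks (Design). Window w = 30 days = 30/7 = 4.29 weeks (Adverse events). Arm size 203 (Power calculation and sample size).

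The arm size reproduces. The diluted effect is 0.38 × (1 − 0.05) = 0.361. At two-sided 5% and 90% power this needs 162 per arm, and 162/(1 − 0.20) = 202.5, rounded up to 203. The point does not depend on this figure; it only scales the person-years below.

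**Assumptions.** The article gives no rate of stopping drug; its 20% is a dropout rate. I assume that 5% to 30% of an arm stops, at times uniform over 72 weeks, and that 50% to 100% of stoppers stay on study.

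**Gap for one participant** who stops at week t and stays to week 72: 72 − t − 4.29 weeks.

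| Stops at week | Weeks uncovered | Share of 72 weeks |
|---|---|---|
| 12 | 55.7 | 77% |
| 24 | 43.7 | 61% |
| 36 | 31.7 | 44% |
| 48 | 19.7 | 27% |

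**Mean gap per stopper who stays**, for uniform stopping times: (T − w)² / (2T) = 67.71² / 144 = 31.8 weeks.

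**Uncovered share of planned arm time** = (proportion stopping) × (proportion of those staying) × 31.84/72.

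- 10% stop, all stay: 0.10 × 0.442 = 4.4%, or 12.4 person-years.
- 20% stop, all stay: 0.20 × 0.442 = 8.8%, or 24.8 person-years.
- Over the whole assumed range: 1.1% to 13.3%, or 3.1 to 37.2 person-years per arm.

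**Recorded event ratio between arms** when the true event rates are equal and constant = (1 − uncovered share, arm A) / (1 − uncovered share, arm B).

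- 20% vs 10% stop, all stay: (1 − 0.0884)/(1 − 0.0442) = 0.954.
- 20% vs 10% stop, half stay: (1 − 0.0442)/(1 − 0.0221) = 0.977.
- 30% vs 10% stop, all stay: (1 − 0.1327)/(1 − 0.0442) = 0.907.
- Equal stopping: 1.00, with events missed in both arms.

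**If recording ran to the last study visit**, the uncovered on-study time would be zero. The sample size would not change.

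**The case against.** The strongest reply is that loss of events is an inference. The article says which events will be recorded; it does not forbid recording later ones. It is a condensed account, the schedule of assessments (Fig 1) is not visible in the text reviewed, and the full protocol may direct sites to take AEs at visits off drug. This stands as a limit on certainty: one can say that later events fall outside the rule, not that they will in fact be lost. It does not remove the point, because the article states the rule itself and nothing shown overrides it.

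A death after stopping would probably also appear as a study withdrawal, and discontinuations are a separate endpoint, so the DSMB would see an imbalance in stopping beside the SAE table. That helps interpretation, but a withdrawal is not counted as an SAE, and a non-fatal SAE has no such second route.

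A reader might infer that the safety comparison is biased in favour of benfotiamine. The documents do not support that. It would need more stopping on active drug, and the article predicts no such difference; its Introduction describes the drug as safe and well tolerated in the pilot trial. The ratios above also concern event totals. Rates per unit of recorded time would be undistorted under the same equal-rate assumption, and a stopper who has already had an event loses nothing on an endpoint that counts participants. The article describes safety summaries, with no formal between-arm test of SAEs.

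A reader might also take the separate naming of AEs and TEAEs in the endpoint as a sign that events off drug were meant to count. The simpler explanation is that AEs run from consent and TEAEs only from first dose.

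**Conclusion.** The point holds as a gap in the collection rule. SAEs and deaths later than 30 days off drug, in participants still in follow-up, are outside what the article says will be recorded, and the phase 2B longer-term safety data are incomplete to that extent.

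The gap is large for an individual who stops early and modest for an arm: about 4% to 9% of planned follow-up if 10% to 20% stop and all of them stay. Any distortion between arms depends on unequal stopping. At an assumed 20% versus 10% the recorded event ratio would be about 0.95 to 0.98, depending on how many stoppers stay. All of these sizes rest on assumed rates of stopping and retention, uniform stopping times and equal, constant true event rates.

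Neither the co-primary efficacy analysis nor the sample size is affected. Recruitment is ongoing (Trial status), and events not collected at the time may be hard to recover later, so the rule is worth correcting now.

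**What to change.** In Adverse events, separate the collection window from the on-treatment definition:

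- Record at least SAEs and deaths, and preferably all AEs, from consent to the later of 30 days after the last dose or the participant's last study visit.
- Keep the 30-day limit for the TEAE definition only.
- Report SAEs and deaths by randomized arm in two ways: on treatment, and over all follow-up.

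If the full protocol already collects these events, the article's sentence should be brought into line with it.

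The cost is a change to one sentence in the protocol and to the case report form guidance, an additional safety table, and a small recording burden at visits that these participants already attend. No visits or procedures are added.
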